### Participants

Participants will be considered for enrollment if they meet the eligibility criteria and have a score of at least 5 on a numeral rating scale(NRS) used to assess overall intensity of CIPN symptoms after completion of chemotherapy for primary breast cancer [28]. Inclusion criteria will be determined by one oncologist and one neurologist. Also, severe CIPN will be determined by the neurologist. More detailed eligibility information on the eligibility criteria is presented in Table 1.

**Table 1 Tab1:** Patient eligibility criteria

Inclusion criteria	Exclusion criteria
Female, at least 19 years old	Patients with a history of receiving chemotherapy for cancer before this diagnosis was made
Patients diagnosed with primary breast cancer	Patients with symptoms of peripheral neuropathy that are severe and need to be immediately treated with surgical procedures or acute management
Patients with a diagnosis of CIPN presenting within the first week of an average pain score of at least 5 on a visual analogue scale of pain after completion of chemotherapy	Patients with pre-existing peripheral neuropathy due to trauma or intercurrent illness
Patients who do not take any medication to prevent or treat neuropathy before screening	Patients with skin inflammation at the attachment site
Patients with an ECOG performance status of 2 or less	Patients with a history of previous use of an acupressure wristband over a week. Patients with a history of cardiovascular disorders including the use of a pacemaker
Patients who are willing and able to comply with the requirements of the study	Patients with known hypersensitivity to metal or any medication
Patients who are willing and able to provide written informed consent	Patients with uncontrolled hypertension (systolic blood pressure ≥ 170 mmHg or diastolic blood pressure ≥ 100 mmHg) or uncontrolled diabetes
	Patients with hepatic insufficiency or dysfunction (three times higher than normal levels of ALT, AST, creatinine)
	Patients who were pregnant or are potentially pregnant and breastfeeding
	Patients with psychiatric disorders or who take medication for psychiatric illnesses
	Patients with a history of receiving investigative, new drugs within 4 weeks before enrollment
	Patients who do not have the ability to read, understand, or respond to questionnaires
	Patients with other reasons not to comply with this study protocol

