### Randomization

A total of 80 participants who meet the eligibility criteria will be randomly assigned in a ratio of 1:1 to the intervention or the placebo control group. The concomitant use of neuropathy medications during the study is a confounding factor that can influence the outcomes of the study. For this reason, the randomization will be stratified according to the use of medication administered for neuropathy. A randomization code list was generated using SAS version V9.4 (SAS Institute Inc., Cary, NC, USA) by a statistician who is not involved in this study. The randomization procedure will be conducted by a research assistant who will not take part in the interview, data collection, intervention, or statistical analysis. Obtaining informed consent and baseline data will be completed before randomization. A link between the randomization code and the corresponding treatment will remain blinded for all other members in the study team.

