### Primary outcome

The primary outcome measure of this study is the overall intensity of CIPN symptoms in women treated with adjuvant chemotherapy for breast cancer. A NRS will be used to assess the overall intensity of CIPN symptoms. This scale is the most widely used clinical tool and its validity has been assessed in studies on patients with cancer [33, 34]. Patients will be asked to rate their symptom intensity on an 11-point scale ranging from 0 (no symptoms) to 10 (worst possible symptoms).

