### Data analysis

Statistical analysis will be performed using SPSS version 22 (IBM SPSS Inc., Chicago, IL, USA) software by a statistician blinded to patient allocation. The efficacy of the intervention will be analyzed using a full analysis set approach with the last-observation-carried-forward method for primary outcome. Demographic and clinical characteristics will be described as frequency and composition ratio. Categorical data will be described as frequency and percentage. Continuous data will be presented by mean and standard deviation or median and interquartile range according to whether the data are normally distributed. For comparison with the baseline outcomes between groups, continuous data will be analyzed by using independent *t* tests or Wilcoxon rank sum tests and categorical data will be analyzed by the chi-squared or Fisher’s exact test. Mean differences from baseline to post treatment in each group will be calculated to evaluate the efficacy of treatment. Analysis of covariance will be used to analyze a difference in primary and secondary outcomes between groups if the residuals are normally distributed, otherwise the Wilcoxon rank sum test will be conducted. Clinically relevant covariates will be included in these analyses. A comparison between responders and non-responders will be conducted to explore heterogeneity of any key variables. A *p* level of 0.05 (two-tailed test) will be considered to indicate statistical significance for all analyses.

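### An undefined residual-normality check decides whether the primary test is ANCOVA or a plain Wilcoxon rank sum test, and the fallback cannot honour the plan's own covariate, stratum and effect-measure statements

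*Protocol article*

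**What the plan says.** All statements are in the protocol article.

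- **Data analysis, test:** "Analysis of covariance will be used to analyze a difference in primary and secondary outcomes between groups", but only "if the residuals are normally distributed, otherwise the Wilcoxon rank sum test will be conducted". No normality test, threshold or graphical criterion is given. Nor does the text say whether the rank sum test would use visit-3 scores or changes.
- **Data analysis, covariates:** the next sentence reads "Clinically relevant covariates will be included in these analyses".
- **Data analysis, effect measure:** "Mean differences from baseline to post treatment in each group will be calculated to evaluate the efficacy of treatment".
- **Data analysis, safeguard:** the statistician is blinded to allocation.
- **Randomization:** neuropathy medication is called a confounding factor, and for that reason "the randomization will be stratified according to the use of medication administered for neuropathy".
- **Sample size:** the trial is sized by a t test on the change in NRS from visit 2 to visit 3, with a difference of 2.33 and an SD of 2.57.
- **Participants and Primary outcome:** patients must "have a score of at least 5 on a numeral rating scale", and the outcome is a whole-number score from 0 to 10.

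No other section fixes the primary test.

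**The concern.** Residuals exist only after the model has been fitted to the outcome data. The ANCOVA result is therefore available when the choice of test is made, and the criterion for that choice is not written down.

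The two branches also answer different questions. ANCOVA estimates an adjusted difference in mean NRS. The rank sum test makes a rank-based comparison with no covariates and no stratum. If the switch occurs, the reported mean change and the primary p-value no longer belong to the same analysis, and the p-value no longer addresses the quantity behind the sample size. What is at stake is certainty, before unblinding, about which test and which effect measure carry the trial's conclusion.

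**Working it through.** **1. The plan's own figure.** Sample size gives n = 2{(z₁₋α/₂ + z₁₋β)σ/Δ}² per group.

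- With 1.96, 1.645, σ = 2.57 and Δ = 2.33: 2 × (3.605 × 2.57/2.33)² = 31.62, hence 32. With the printed 1.64 it is 31.53. The stated 32 reproduces.
- Power by normal approximation is Φ(Δ/(σ√(2/n)) − 1.96). For n = 32: Φ(3.63 − 1.96) = 95.2%. For n = 40: Φ(4.05 − 1.96) = 98.2%.

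So the trial is sized on a difference in mean change.

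**2. The two branches against the plan's other statements.**

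| Statement in the plan | ANCOVA | Rank sum test |
|---|---|---|
| Covariates included | yes | not possible |
| Medication stratum | can be a term | ignored |
| Baseline NRS | can be a covariate | only by subtraction, if changes are ranked |
| Mean change as the efficacy measure | tested | not tested |
| Same quantity as the sizing | yes | no |

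With baseline as a covariate, the ANCOVA arm coefficient is the same whether the response is the visit-3 score or the change. ANCOVA of the visit-3 score therefore stays consistent with the sizing.

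**3. What the switch does.** The documents give no residual distribution, so these inputs are assumptions: 40 per group; baseline 5 to 10 (mean about 6.5); control mean about 4.5 at visit 3; slope 0.7 on baseline; error SD 2.4 before rounding and truncation to 0-10; medication effect 0 or 1.5 points; errors normal or right-skewed (gamma). ANCOVA adjusts for baseline and stratum, and the rank sum test is on change. The trigger is Shapiro-Wilk p < 0.05, which the protocol does not name. There were 4,000 trials per scenario. Ranges cover the two medication effects; entries are % of trials, and the middle three columns are % significant.

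| Errors | Difference | Switches | ANCOVA | Rank sum | Stated rule | Tests disagree |
|---|---|---|---|---|---|---|
| Normal | 0 | 6.8-7.0 | 4.8-5.2 | 4.2-4.8 | 5.0-5.1 | 2.3-2.6 |
| Normal | 1.2 | 11.0-11.7 | 58.4-59.2 | 51.8-57.0 | 58.0-59.0 | 9.2-10.6 |
| Normal | 2.33 | 15.3-17.2 | 98.6-98.9 | 97.5-98.5 | 98.5-98.8 | 0.9-1.4 |
| Skewed | 0 | 95.2-95.4 | 4.8-4.9 | 3.9-4.4 | 4.0-4.5 | 2.5-3.0 |
| Skewed | 1.2 | 97.2 | 60.1-62.1 | 61.1-69.2 | 61.2-69.4 | 11.4-13.4 |
| Skewed | 2.33 | 97.9-98.4 | 98.3-98.6 | 99.0-99.6 | 98.9-99.6 | 1.2-1.4 |

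**4. Sensitivity to the control-arm improvement.** This is also assumed (SD 2.2, slope 0.7, 2,000 trials per scenario). With normal errors, the rule switches in 4-9% of trials for a 1.5-point control improvement, 8-21% for 2.5 points and 26-50% for 3.5 points. With skewed errors it switches in about 100%. At a 1.5-point treatment effect with normal errors, the rule has 83%, 84% and 79% power for the three improvements, against 83%, 84% and 80% for ANCOVA throughout. With skewed errors the rank sum test on change has 91-97% against 79-89% for ANCOVA.

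**5. Reading.** How often the rule switches cannot be predicted from the documents. With normal errors it also rises with the treatment effect (about 7% at no effect, 15-17% at 2.33), because more patients reach the floor at 0.

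**The case against.** The case for leaving the rule alone has real content. The statistician is blinded. The rule keeps its type I error. At 2.33 both tests have high power and seldom disagree. If errors are skewed, the fallback can be the more powerful test. A rank sum test on changes still uses baseline by subtraction, so baseline information is not wholly lost; what goes is regression on baseline, the stratum and the other covariates. All of this stands.

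Three stronger readings are tempting, and the documents do not support them:

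- **Inflated type I error.** The simulated rule stays at 4.0-5.1%.
- **A general loss of power.** The rule uses the rank sum test only in trials that switch, so comparing the two tests over all trials overstates the cost. With normal errors the rule loses at most about 1 point.
- **A switch close to a coin flip.** That needs a control improvement of about 3.5 points with normal errors. No section gives a control-arm change: the −4.0 in Sample size is an overall change in a published electroacupuncture study.

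What the objection does not answer is the wording. Blinding does not define the normality check or choose between the tests, and it does not make a rank sum test accept covariates. Nor is this detail that an article leaves to an analysis plan: the article states the rule outright, so a plan naming one test would have to override it.

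**Conclusion.** The point holds as a defect of specification that should be corrected. An undefined check on the trial's own outcome data selects the primary test. The fallback contradicts the covariate sentence, ignores the randomization stratum and does not test the difference in mean change. These conclusions follow from the text and need no simulation.

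The numerical consequence is modest and uncertain. Across the assumed scenarios the switch occurs in roughly 5% (4% at the lowest) to nearly 100% of trials. The tests disagree in about 9-13% of trials at a difference of 1.2, but only in up to about 2% at 2.33. These figures rest on assumed distributions and an assumed Shapiro-Wilk trigger, so they show how unpredictable the rule is and do not forecast this trial.

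**What to change.** State that the primary analysis is ANCOVA of the visit-3 NRS on arm, baseline NRS and medication stratum, whatever the residuals look like. Any further covariates should be named in advance. Robust or bootstrap standard errors are optional: in the runs above, ordinary ANCOVA kept its type I error at 4.8-5.2% with 40 per group. Report a stratified rank test (van Elteren) or rank ANCOVA as sensitivity only, and apply the same rule to the secondary scores.

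The cost is one sentence, settled before unblinding; the article reports recruitment as ongoing. The sample size does not change. The downside is that, with strongly skewed errors, ANCOVA may have somewhat less power than the rank test (60-62% against 61-69% at a difference of 1.2). At the design difference its power stayed above 95% in the scenarios run.

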### Secondary outcomes

The key secondary outcome variables include physician-rated symptom severity assessed by the Total Neuropathy Score (TNS), patient-reported CIPN symptom distress level tested with a self-rated questionnaire and, and perceived HRQOL, and the instrument for pattern identification and evaluation for CIPN.

The TNS will be used to assess the presence, severity, and location of symptoms. This scale was originally developed to evaluate diabetic neuropathy and later validated in cancer patients with peripheral neuropathy [35, 36]. The TNS can provide combined information obtained from pin-prick, vibration threshold, and nerve conduction studies. The TNS (range 0 to 40) combines 10 items of symptom scores, including sensory, motor, autonomic symptoms, pin sensibility, vibration sensibility, and deep tendon reflexes [37, 38]. Each neuropathy item will be scored by a neurologist on a 0 to 4 scale. The reliability and validity of this scale were determined in various studies in patients with CIPN [36, 37, 39].

The Functional Assessment of Cancer Therapy-Breast (FACT-B) will be administered to measure the primary domains of wellbeing (i.e., physical, social/family, emotional, and functional wellbeing) and a breast cancer-specific subscale that assesses symptoms and concerns related to breast cancer [40]. The FACT-B is a 37-item measure and has demonstrated good reliability, validity, sensitivity, and suitability for use in various international studies [41–43].

The European Organization for Research and Treatment of Cancer Quality of Life (EORTC-QLQ) Chemotherapy-Induced Peripheral Neuropathy 20 (CIPN20) will be used to evaluate patients’ experience of symptoms and functional limitations related to CIPN. This instrument consists of three subscales: (1) sensory (nine items), (2) motor (eight items), and (3) autonomic (three items) symptoms and functioning. Each item is rated on a 4-point Likert scale ranging from 1 (not at all) to 4 (very much) [8]. The CIPN20 was established as a reliable and valid measurement tool for individuals with CIPN [44, 45].

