The instrument of pattern identification and evaluation for CIPN will be used to diagnose and evaluate CIPN based on the perspective of traditional oriental medicine [46]. This instrument includes 30 items, which can be divided into four patterns such as wind arthralgia, cold arthralgia, dampness arthralgia, and arthralgia of the deficiency type. All items are scored by an oriental medicine physician on a 5-point Likert scale and higher scores indicate greater distress in each CIPN pattern.

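### An unadjusted 0.05 significance rule covers all analyses, including four key secondary instruments, so the chance of a falsely significant key secondary result is well above 5%

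*Protocol article*

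**What the plan says.** Under Primary outcome, the protocol article names a single measure: "The primary outcome measure of this study is the overall intensity of CIPN symptoms", rated on the NRS. The Sample size section rests on that outcome alone.

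Under Secondary outcomes it begins: "The key secondary outcome variables include physician-rated symptom severity assessed by the Total Neuropathy Score (TNS"). It then adds the self-rated CIPN distress questionnaire (CIPN20), health-related quality of life (FACT-B) and the pattern-identification instrument. That makes four instruments, all labelled key. Their parts are described as follows:

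- TNS: "The TNS (range 0 to 40) combines 10 items of symptom scores", so one total score.
- FACT-B: four domains plus one subscale ("physical, social/family, emotional, and functional wellbeing) and a breast cancer-specific subscale"), so five scores.
- CIPN20: "This instrument consists of three subscales: (1) sensory (nine items), (2) motor (eight items), and (3) autonomic (three items"), so three scores.
- Pattern instrument: "This instrument includes 30 items, which can be divided into four patterns", so four scores.

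Under Data analysis, primary and secondary outcomes are both compared between groups by analysis of covariance, or by the Wilcoxon rank sum test if residuals are not normal. The significance rule is then set once for everything: a p "level of 0.05 (two-tailed test) will be considered to indicate statistical significance for all analyses". The article gives no order of testing, no adjustment, no condition that the NRS succeed first, and no statement that secondary results are supportive only.

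**The concern.** This is a stated rule, not a detail left for later. It gives each key secondary outcome the same criterion for significance as the primary outcome. A later analysis plan that controlled the error rate over the secondary outcomes would have to depart from it.

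What is at stake is the reading of an isolated secondary result. The Discussion says that no definitive tool for evaluating CIPN exists and that several tools will therefore be used, and quality of life is part of the stated purpose. If the NRS comparison were null and one of the other instruments reached p < 0.05, the plan as written would let that result be called statistically significant. Nothing in the article would tell the reader that the chance of at least one such result, with no effect at all, is well above 5%.

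**Working it through.** **The plan's own figure.** The article states no error rate over several outcomes. Its only related figure is the sample size for the NRS, with Δ = 2.33, SD = 2.57, two-sided 0.05 and 95% power:

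- n = 2 × [(1.96 + 1.64) × 2.57 / 2.33]² = 31.53 per group, or 31.62 with unrounded normal quantiles. The article prints 31.63.
- All three round up to 32. The 0.05 in this calculation belongs to one test on one outcome.

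**Inputs for the check.**

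- Level per test: 0.05, two-sided (Data analysis).
- Fewest secondary tests considered: 4, one per key instrument (Secondary outcomes).
- All secondary scores described: 1 (TNS) + 5 (FACT-B) + 3 (CIPN20) + 4 (patterns) = 13.
- Number of tests actually planned: not given, so 4 to 13 is an assumed range.
- Correlation between test statistics: not given. Values from 0 to 0.8 are assumed.

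**Independent tests.** With k tests at 0.05 and no effect on any outcome, the chance of at least one significant result is 1 − 0.95^k:

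- k = 4: 1 − 0.95^4 = 18.5%.
- k = 9 (FACT-B reduced to one score, so 1 + 1 + 3 + 4): 1 − 0.95^9 = 37.0%.
- k = 13: 1 − 0.95^13 = 48.7%.

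**Correlated tests.** The scores come from the same patients and overlap in content, so positive correlation is likely. The chances below were simulated with normal test statistics sharing one common correlation r (400,000 draws per cell), except the r = 0 column, which is the formula above.

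| Secondary tests | r = 0 | r = 0.2 | r = 0.3 | r = 0.5 | r = 0.7 | r = 0.8 |
|---|---|---|---|---|---|---|
| 4 | 18.5% | 18.0% | 17.5% | 15.6% | 13.0% | 11.5% |
| 13 | 48.7% | 45.2% | 41.9% | 33.4% | 24.1% | 19.2% |

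Letting scores correlate more within an instrument (0.5 to 0.7) than between instruments (0.2 to 0.4) gives 34.4% to 41.0% for 13 tests.

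**With an adjustment.** Bonferroni over four tests uses 0.05 / 4 = 0.0125 each. If independent, the chance of any false positive is 1 − (1 − 0.0125)^4 = 4.9%. Holm also keeps this chance at or below 5%, with at least as much power.

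**The primary outcome.** It is one pre-specified test at 0.05. Its false-positive chance stays at 5% however many secondary tests follow.

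**The case against.** The strongest reply is that the trial has one primary outcome, that the hypotheses and sample size are written for it alone, and that nothing in the article says efficacy may rest on a secondary result. Unadjusted secondary outcomes are common and acceptable when they are supportive. A journal article condenses the protocol, and a hierarchy or a supportive label may stand in a document not shown. The Sample size section also describes the trial partly in pilot and feasibility terms, for which a full confirmatory scheme could be excessive.

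Much of this stands. The primary conclusion is safe, the absence of a detailed testing scheme would not by itself be a finding, and gated Holm testing is an option rather than a necessity. The reply does not remove the rule that the article does state: significance at 0.05 for every analysis, applied to outcomes labelled key, without the supportive label that would make it harmless.

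A reader might also infer something stronger: that the plan expressly permits a significance claim on every subscale, that about 14 tests are planned, and that a chance significant key secondary is therefore about as likely as not. The article does not support this. It describes subscales as parts of the questionnaires and never says that each will be tested; it merely does not exclude it. A count of 14 includes the NRS, so the described secondary scores number 13. A chance near one half also needs all 13 to be tested and to be independent, which is implausible for overlapping scores from the same patients.

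**Conclusion.** The point holds for claims on secondary outcomes only. Under no effect, the plan's rule gives a chance of at least one falsely significant key secondary of:

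- up to 18.5% with one test per instrument, and 11.5% to 15.6% at assumed correlations of 0.8 to 0.5;
- up to 48.7% if all 13 described scores are tested, and 19.2% to 33.4% at the same assumed correlations.

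The number of tests and the correlations are assumptions, because the article gives neither. In every scenario computed, the chance is more than twice the nominal 5%. It would be wrong to infer that the trial's main conclusion is affected, since the NRS test keeps its 5% level. This is a cheap improvement to the wording and does not challenge the design.

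**What to change.** In Data analysis, replace the sentence that applies 0.05 to all analyses. Reserve the two-sided 0.05 significance claim for the between-group comparison of the primary NRS outcome. State that all secondary outcomes and their subscales will be reported as supportive estimates of the group difference with 95% confidence intervals and no claim of significance.

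If the sponsor wants confirmatory secondary claims, name one score per instrument in advance and test these four by Holm at an overall 0.05, only if the NRS result is significant. This option needs scores to be defined first, because the article describes CIPN20 by its three subscales and the pattern instrument by its four patterns, and gives no total for either.

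The cost is a change of wording, best made before unblinding. Sample size, visits and data collection do not change. The downside is that fewer secondary results can be called significant.
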